## Study Design

A three-arm open label randomised control non-inferiority trial of RDT screening with or without treatment with SP or AQ+AS versus IPTp using SP as follows: -

1. OptiMAL® antigen screening and treatment with SP plus LLIN
2. OptiMAL® antigen screening and treatment with AQ+AS plus LLIN
3. SP-IPTp plus LLIN

## Study site and population

The study will be conducted in the Ejisu-Juaben and Sekyere East districts of the Ashanti Region of Ghana. Enrolment will be done simultaneously at the antenatal clinics of the Effiduase and Juaben district hospitals and a sub district health centre in each of the districts. The Effiduase and Juaben hospitals have 50 and 40 beds respectively and provide all basic medical services including adult medicine, paediatrics, surgery and obstetrics and gynaecology. They run weekly antenatal clinic sessions and together they register an average of 220 new pregnant women per month. The sub district health centres (at Kwaso and Kumawu) are manned by qualified medical assistants and midwives. Together they register an average of 80 new pregnant women per month. All health facilities in the study districts including the proposed enrolling clinics offer SP-IPT to pregnant women following the MoH guidelines. Pregnant women in their second or third trimester diagnosed with malaria are treated with AQ+AS as recommended by the MoH at these facilities. The study population will comprise pregnant women presenting at the hospital’s antenatal clinic with a gestation of 16 to 24 weeks at their first booking.

## Enrolment Procedures

A schematic profile of the study is shown in Figure 1. All study pregnant women will be recruited from weekly antenatal clinic sessions held at the study sites over a period of one and half years. Three teams of midwives and their assistants put together and trained by the principal investigator (PI) will assist the PI and research teams to conduct the recruitment during antenatal clinic hours. The standard operating procedures at the clinic will be as follows:

1. Randomise pregnant women reporting at the ANC who consent to participate in the study into three arms: an IPTp arm, RDT screening and SP case management arm and RDT screening and AQ+AS case management arm. Distribute LLIN to eligible pregnant women in all arms.
2. Obtain blood for baseline investigations including haemoglobin level, thin and thick blood films for malaria parasite counts and, filter paper blood spots.
3. Assess all pregnant women in the RDT and treatment groups clinically and obstetrically prior to OptiMAL® dipstick screening; for those parasitaemic offer SP or AQ+AS and ingestion of first dose observed directly at the ANC. Encourage the women to regularly sleep under the bed nets provided and take their daily doses of iron and folic acid tablets.
4. For women in the RDT and treatment groups who are negative offer only daily doses of iron and folic acid tablets and encourage them to regularly sleep under the bed nets provided.
5. Women in the IPTp group will receive SP and ingestion directly observed at the ANC according to the national guideline. Encourage the women to regularly sleep under the bed nets provided and take their daily doses of iron and folic acid tablets.
6. Women who decline participation in the study will receive SP-IPTp according to the national guideline.

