**Exclusion Criteria**

A pregnant woman will not be eligible for inclusion in the study if: -

1. She has a past obstetric and medical history that will adversely affect the interpretation of outcomes such as repeated stillbirths and eclampsia.
2. She has a haemoglobin level below 5.0 g/dl.
3. She has malaria that is severe enough to require parenteral medication.

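### The enrolment steps list open-label randomisation before the haemoglobin sample, and before a clinical and obstetric assessment worded only for the RDT groups, although exclusion criteria draw on these findings

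*Protocol*

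**What the plan says.** The Study Design section describes "A three-arm open label randomised control non-inferiority trial of RDT screening", so staff know the arm once it is assigned.

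The Enrolment Procedures section gives a numbered sequence for the clinic:

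- Step 1: "Randomise pregnant women reporting at the ANC who consent to participate in the study into three arms". Consent is the only condition named. The same step continues: "Distribute LLIN to eligible pregnant women in all arms".
- Step 2: "Obtain blood for baseline investigations including haemoglobin level, thin and thick blood films for malaria parasite counts". This is not restricted to any arm.
- Step 3: "Assess all pregnant women in the RDT and treatment groups clinically and obstetrically prior to OptiMAL® dipstick screening". This is restricted to the RDT groups.
- Step 5 takes the IPTp group to directly observed SP and names no clinical or obstetric assessment.

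The flow chart (Figure 1) names gestation as the only condition at randomisation and labels the IPTp arm as unscreened.

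The Exclusion Criteria list three grounds: a past obstetric or medical history that would disturb interpretation of the outcomes; "She has a haemoglobin level below 5.0 g/dl"; and "She has malaria that is severe enough to require parenteral medication".

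The protocol describes no separate eligibility step before step 1. It does not say what happens to a woman found to meet an exclusion after she has been allocated.

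**The concern.** Eligibility should be settled before allocation, by the same checks in every woman. In the listed order, one exclusion depends on a sample taken after allocation. The only clinical and obstetric assessment described also comes after allocation, and only in two of the three arms. Because the trial is open label, whoever judges eligibility at that point knows the arm.

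The primary outcome is haemoglobin below 8 g/dl at 34 to 36 weeks. Women with very low haemoglobin or severe malaria at booking plausibly carry a higher risk of it. If such women were found and dropped more often in the RDT arms than in the IPTp arm, severe anaemia would look rarer under screening, and the result would move towards non-inferiority, which is what the trial sets out to show. Both RDT arms would share the bias, so agreement between them would not reveal it.

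**Working it through.** **Exclusions against steps**

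| Exclusion | Where the finding arises in the listed steps | Arms |
|---|---|---|
| Haemoglobin below 5.0 g/dl | Step 2, after allocation | All three |
| Malaria needing parenteral drugs | Clinical assessment in step 3, after allocation (blood films in step 2 cover all arms) | Assessment specified for the RDT arms only |
| Adverse obstetric or medical history | Not stated; could be taken at booking or in step 3 | Unclear |

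The haemoglobin criterion is therefore applied late but evenly. Any imbalance between arms has to come from the second criterion and possibly the third.

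**The plan's own figure**

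Inputs from the Sample size section: 12% severe anaemia expected in the IPTp arm, a margin of 5 points, 90% power, and 95% significance read as one-sided 0.025.

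n = 2 × 0.12 × 0.88 × (1.960 + 1.282)² / 0.05² = 888 per arm, against 887 stated. With 20% dropout, 888 / 0.8 = 1110, as stated. The point does not depend on this figure, but it supplies the standard error used below.

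**Illustration of size (assumptions, not protocol figures)**

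Let x be the fraction of an RDT arm removed after allocation with no matching removal in the IPTp arm, and let r be the risk of severe anaemia among the women removed. Put the RDT arm truly at the margin, 17% against 12%, where the one-sided error should be 2.5%.

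- RDT prevalence after removal = (0.17 − x·r) / (1 − x)
- Standard error of the difference = √[(0.12 × 0.88 + 0.17 × 0.83) / 888] = 1.667 points
- Type I error = Φ(−1.96 + shift / 1.667), with the shift in points

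With r = 50%:

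| x | RDT prevalence after removal | Shift (points) | Type I error |
|---|---|---|---|
| 0 | 17.0% | 0 | 2.5% |
| 0.2% | 16.9% | 0.07 | 2.7% |
| 1% | 16.7% | 0.33 | 3.9% |
| 2% | 16.3% | 0.67 | 6.0% |
| 3% | 16.0% | 1.02 | 8.9% |

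Varying r from 30% to 80% (887 per arm, standard error recomputed after removal) gives 3.0% to 5.8% at x = 1%, and 3.6% to 11.9% at x = 2%.

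The direction depends on r. The shift equals x(r − 0.17)/(1 − x), so it favours non-inferiority only if the women removed have a risk above 17%. That is plausible for severe malaria. The documents give no basis for it in women excluded for obstetric history.

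**The case against.** A reader might infer that, as written, sicker women are excluded after allocation and from the RDT arms alone. The protocol does not support that, for these reasons:

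- No section says that a woman is withdrawn, replaced or left out of the analysis after allocation. The exclusions are worded as conditions of entry. Who stays in the analysis set is commonly left to the SAP, which is not at hand.
- Step 1 speaks of eligible women in all arms, which suggests that the authors took eligibility as settled by then.
- Step 1 cannot be a full account of the checks before randomisation. It omits gestation, residence and willingness to deliver in the district, although the Inclusion Criteria require all three and Figure 1 places gestation before allocation.
- Haemoglobin and blood films are taken in every arm, so the exclusion closest to the primary outcome creates no one-sided removal by itself.
- Obstetric history can be asked of anyone at first booking. Step 3 reads as preparation for the RDT and the treatment decision and does not mention eligibility. The unscreened label on the IPTp arm may refer to RDT screening alone.
- The removal fractions and the 50% risk are not in the documents, and at 0.2% the effect is negligible.

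All of this stands, and it limits the claim. It does not remove the problem of order. No earlier haemoglobin measurement is described, so on the stated sequence the haemoglobin criterion cannot be applied before the arm is known. The one clinical assessment described is not specified for the IPTp arm. An analysis plan can say who is kept, but it cannot supply an assessment that was not made in one arm.

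**Conclusion.** The concern holds as a defect of sequence. The listed steps place the haemoglobin exclusion after a known allocation in all arms. They also allow severe malaria, and possibly adverse history, to be detected more often in the RDT arms. If women found ineligible were then dropped, the comparison could be biased towards non-inferiority.

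The protocol establishes neither that women would be removed nor that removal would be confined to the RDT arms. The size cannot be derived from it. The range of about 2.7% to 8.9% for the one-sided error, against 2.5%, rests on three assumptions: 0.2% to 3% of RDT-arm women removed, no matching removal in the IPTp arm, and a 50% risk of severe anaemia among those removed. At the low end the effect hardly matters. The text should be corrected because the change is cheap before recruitment and an imbalance in who was assessed cannot be repaired afterwards. It is not evidence that the planned comparison is invalid.

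**What to change.** Reorder the Enrolment Procedures and Figure 1 as follows:

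1. Obtain consent.
2. Take haemoglobin, blood films and history, and carry out the clinical and obstetric assessment, identically in every woman.
3. Apply all inclusion and exclusion criteria.
4. Randomise.
5. Carry out OptiMAL testing in the RDT arms, and proceed with the IPTp arm as already planned.

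If the order cannot be changed, state that every randomised woman stays in the primary analysis whatever is found afterwards. This concerns the analysis set and not her clinical care.

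The cost is a short booking assessment for women who go on to the IPTp arm and slightly more work before allocation. The sample size stays at 1110 recruited per arm.

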**Inclusion Criteria**

A pregnant woman will be eligible to be included in the study if: -

1. Her pregnancy is confirmed at 16 to 24 weeks at their first booking.
2. She is willing to participate and complete the test schedule, and has given informed consent.
3. She is willing to have supervised delivered at maternity units in the district.
4. She lives within the study district.

**Exclusion Criteria**

A pregnant woman will not be eligible for inclusion in the study if: -

1. She has a past obstetric and medical history that will adversely affect the interpretation of outcomes such as repeated stillbirths and eclampsia.
2. She has a haemoglobin level below 5.0 g/dl.
3. She has malaria that is severe enough to require parenteral medication.

## Antenatal Follow-Up Procedures

1. **Day 7:** Women receiving SP or AQ+AS treatment will be followed up actively on the day 7 post treatment to assess any adverse events during the week post treatment.
2. **At 6 months:** repeat SP-IPT for women in the IPT arm and treat women in the case management with SP or AQ+AS if they are RDT positive. Women in the case management arm with negative RDT would receive only haematinics. Ask all study women to regularly sleep under bed nets provided.
3. **At 8 months:** repeat SP-IPT for women in the IPT arm and treat women in the case management with SP or AQ+AS if they are RDT positive. Women in the case management arm with negative RDT would receive only haematinics. Ask all study women to regularly sleep under bed nets provided.
4. **At 34 to 36 weeks:** actively follow up women to sample blood by finger prick for haemoglobin measurements, slide smears for malaria parasite counts and filter paper blood spots.
5. **Unscheduled visits:** Women presenting with a history of fever during an unscheduled visit will be tested for malaria parasite. If they were found parasitaemic, they will be deemed to be treatment failure and will be treated with quinine as rescue medication.
6. All pregnant women would receive haematinics packs at each of the follow ups.

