There is currently great international support and momentum to increase the coverage of ITNs use among pregnant women. Thus while looking for alternative drugs for IPT in areas with SP resistance we have to consider the additional benefits of the combination of ITN and IPT over ITN with effective case management approach and the potential drug related adverse outcomes of drugs used for IPTp. The RDT screening and treatment with an effective antimalarial of those with a positive RDT test will reduce the number of women that would be exposed to drugs. Although some women with placental malaria may be missed by the RDT screening, it can be argued that the proportion of women with placental malaria missed by RDT would be minimal if all women used an ITN and that the risk of missed placental malaria will be offset by the reduction in women exposed to antimalarials of uncertain safety profile unnecessarily.

We are proposing this follow up study to determine whether active case finding and management is as effective as intermittent preventative treatment for the control of malaria during pregnancy. A two-armed non-inferiority randomised trial using SP in both arms (LLIN+ IPTp or LLIN + RDT & treatment) is appropriate to address this question. However, if SP is not very effective, a difference may not be found between the two arms since the effect of SP as IPT or treatment would be minimal and the effect of LLIN would be similar in both arms. We cannot replace SP with another effective antimalarial in the IPTp arm since the safety profile of potential antimalarial drugs that could replace SP are not adequately established to be useful for IPTp. A two arm study of LLIN + SP-IPTp and LLIN + RDT & AQ+AS treatment will not be appropriate to prove the principle that LLIN + RDT & treatment is not inferior to LLIN + IPTp since AQ+AS is likely to be more efficacious than SP and this would bias our observation. Thus we propose a three arm trial: (1) LLIN plus SP-IPTp; (2) LLIN plus RDT and treatment with SP (3) LLIN plus RDT and treatment with AQ+AS.

AS+AQ is the first line drug of choice for treatment of uncomplicated malaria in Ghana. However there is very little safety data on the use of AS+AQ for the treatment of malaria during pregnancy and the safety data collected in this study will be very useful for informing the national drug policy for treatment of malaria during pregnancy.

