## Delivery and Postpartum Follow-up

1. The midwives will record all birth weights and note any stillbirths and perinatal deaths.
2. Midwives will record all congenital deformities for verification and confirmation by a clinician.
3. Visit all women and babies at 6 to 8 weeks post delivery to obtain reports of any neonatal adverse events such as deaths or morbidity.
4. At 6 weeks post partum, if a woman has peripheral parasitaemia she will be treated with SP and followed up for parasite clearance on days 14 and 28 post treatment. If there is no parasite clearance on day 14 and/or day 28 a course of rescue medication (quinine) will be given. This part of the study is necessary to assess the efficacy of SP to clear parasitaemia.

Figure 1: - Flow chart of proposed study design

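### During pregnancy, maternal adverse events are actively sought only in women who were dosed, so maternal adverse event counts cannot be compared between randomised arms

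*Protocol*

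**What the plan says.** Protocol, Antenatal Follow-Up Procedures, item 1, sets the day 7 check: "Women receiving SP or AQ+AS treatment will be followed up actively on the day 7 post treatment to assess any adverse events". Items 2 and 3 of the same section (6 and 8 months) deal with repeat SP, repeat screening, haematinics and net use. Item 4 (34 to 36 weeks) is an active contact for blood sampling. None of these items asks about adverse events.

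Who is dosed differs by arm. In the IPTp arm, "Women in the IPTp group will receive SP and ingestion directly observed at the ANC according to the national guideline" (Enrolment Procedures, step 5). In the screening arms, step 4 says "For women in the RDT and treatment groups who are negative offer only daily doses of iron and folic acid tablets", and the follow-up items repeat this: "Women in the case management arm with negative RDT would receive only haematinics". Women found parasitaemic at an unscheduled fever visit form a further group: "they will be deemed to be treatment failure and will be treated with quinine as rescue medication" (Antenatal Follow-Up Procedures, item 5).

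The Background & Rationale rests part of the case for screening on drug exposure. Screening "will reduce the number of women that would be exposed to drugs", and it argues that "the risk of missed placental malaria will be offset by the reduction in women exposed to antimalarials of uncertain safety profile unnecessarily".

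After delivery, follow-up does not depend on dosing: "Visit all women and babies at 6 to 8 weeks post delivery to obtain reports of any neonatal adverse events" (Delivery and Postpartum Follow-up, item 3).

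**The concern.** Whether a woman is asked about adverse events depends on whether she was dosed, and dosing is what the arms are designed to vary. Ordinary complaints of pregnancy will be recorded in dosed women and go unrecorded in undosed women. RDT-negative women supply no background rate against which to judge what dosed women report.

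The wording is also open on a point that decides the direction of the distortion. Item 1 speaks of SP or AQ+AS treatment. Items 2 and 3 speak of repeating SP-IPT in one arm and of treating women in the others. Clinics could reasonably differ on whether a preventive SP dose triggers the day 7 contact, and on whether the contact recurs after each later dose.

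At stake is the maternal side of the exposure argument. The trial would show how many women were spared a drug. It would have no like-for-like evidence on whether that spared them adverse events.

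**Working it through.** **1. Who is asked in pregnancy, from the text.**

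| Group | Drug received | Active adverse event enquiry |
|---|---|---|
| IPTp arm | SP, all women | Day 7 if a preventive dose counts as treatment; otherwise none |
| Screening arms, RDT positive | SP or AQ+AS | Day 7 |
| Screening arms, RDT negative | Haematinics only | None |
| Any arm, parasitaemic at a fever visit | Quinine | None triggered by the quinine course |

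**2. The protocol's own figure.** It gives no adverse event rate, so there is none to reproduce. The only figure borrowed here is the arm size, which does reproduce. With 12% in both arms, a margin of 5 percentage points, one-sided 0.025 and 90% power, n = (1.960 + 1.282)² × 2 × 0.12 × 0.88 / 0.05² ≈ 888 (stated: 887), and 888 / 0.80 = 1110 (stated: 1110). The sample size has no bearing on the point.

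**3. Illustration with no drug effect.** The protocol gives neither RDT positivity nor a background complaint rate, so both are assumed. Let N = 1110 per arm, r = 10% of women with a complaint in any given week, and q = proportion RDT positive. Take one dosing round with IPTp doses covered by the day 7 check.

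- IPTp reports = N × r = 1110 × 0.10 = 111.
- Screening-arm reports = N × q × r.
- Ratio = (N × r) / (N × q × r) = 1/q, whatever the value of r.
- Women not asked in a screening arm = N × (1 − q).

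| Assumed q | IPTp reports | Screening-arm reports | Ratio | Not asked per screening arm |
|---|---|---|---|---|
| 10% | 111 | 11.1 | 10 | 999 |
| 20% | 111 | 22.2 | 5 | 888 |
| 40% | 111 | 44.4 | 2.5 | 666 |

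The true ratio is 1 in every row. At r = 5% or 20% the counts halve or double and the ratios do not move.

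**4. The other reading.** If preventive doses do not count as treatment, the IPTp column is 0 against 11.1, 22.2 or 44.4, and the arm in which every woman is dosed contributes no reports.

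**5. Does reporting per course restore the comparison?** It removes the 1/q factor. It does not make IPTp comparable with screening, because it sets unselected women against women selected for being parasitaemic, whose malaria symptoms may fall in the same week. SP against AQ+AS among women positive at the first screen is a fair comparison. At later screens, being positive is a post-randomisation event that earlier treatment may have influenced.

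**The case against.** The strongest reply is that no listed analysis is damaged. Specific objectives and Study outcomes include no between-arm comparison of maternal adverse events in general. The safety gap that the Background & Rationale names is the use of AS+AQ to treat malaria in pregnancy, and a day 7 check in treated women suits that. The inflated ratio appears only if someone divides day 7 reports by all randomised women, which the protocol does not propose, and denominators can be left to a statistical analysis plan. All of this stands, and it limits the weight of the point. It does not dispose of it, because an analysis plan can choose a denominator but cannot recover events nobody asked about.

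Three stronger readings are tempting, and the protocol does not support them.

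- A reader might infer that day 7 is the only active adverse event contact in the whole trial. It is not: all women and babies are visited at 6 to 8 weeks after delivery for neonatal events, in every arm.
- A reader might infer that the arms cannot be compared at all on the safety trade-off. They can in large part. Pregnancy loss, stillbirth, neonatal and maternal mortality, pre-term delivery, congenital anomalies and placental parasitaemia are planned outcomes whatever the dosing, and the number of women exposed can be counted in each arm.
- A reader might infer that SP's long half-life means late events are being missed. The protocol mentions half-life only when explaining why SP is hard to replace for IPTp. It says nothing about the timing of adverse events.

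It is also fair to say that the natural reading of item 1 may include IPTp women, since the abbreviation itself contains the word treatment. That makes the zero-count branch less likely, but the text still has to settle it.

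**Conclusion.** The point holds for maternal adverse events during pregnancy. They are actively sought only after SP or AQ+AS, so counts by arm reflect who was dosed and do not estimate a difference between strategies. If IPTp doses are covered, the raw ratio in one round with no drug effect is 1/q, that is 10, 5 or 2.5 at 10%, 20% or 40% positivity. These positivity values are assumptions, and the ratio describes a raw by-arm count, not a planned analysis. If IPTp doses are not covered, that arm has no counts.

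The primary outcome and every listed delivery, neonatal, mortality, anomaly and placental outcome are untouched. This is an inexpensive improvement in data collection that would give the trial a maternal safety comparison by randomised arm, which it now lacks. It has to be made before the data are collected.

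**What to change.** - Add to Antenatal Follow-Up Procedures, items 2 to 4, and to the delivery record, one identical question on adverse events and hospital admissions since the last contact. Ask it of every woman in all three arms, whatever her RDT result or treatment, and use it for any between-arm comparison of maternal safety.
- Keep the day 7 contact as a tolerability check, reported per course and not per arm.
- State in item 1 whether the day 7 contact covers each SP-IPT dose, whether it recurs after the 6 and 8 month rounds, and whether it covers quinine courses.

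No dose, schedule or rescue rule changes. The cost is one form page, a few minutes per visit, and more day 7 contacts if preventive and quinine courses are brought in.

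The limits should be acknowledged. Recall fades between visits, which can be about two months apart, so the question will not measure short-term tolerability well. The flow chart calls the 6, 8 and 9 month follow-up passive, so some answers will be missing. The trial is open label, so dosed women may still report more under identical wording. An active day 7 contact with every woman after every round would time the enquiry equally, but at much greater cost.
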